### Power and sample size

In the previous ARCHES study conducted among private sector FP clients in Nairobi, incident unintended pregnancy at six months post-intervention, the primary outcome for the present study, was 1.72% among those receiving ARCHES and 3.13% among those receiving standard-of-care FP care (AOR 0.54) (unpublished). The present study is powered to detect an AOR of 0.54 in unintended pregnancy in the intervention group compared to the control group at an alpha of 0.15, assuming intra-class correlation of 0.1 from the previous trial (unpublished) and a six-month retention rate of 80% (6-month retention rate of 82% achieved in the previous trial, unpublished). Based on these assumptions, 1770 FP clients are needed at baseline enrollment per study arm (3540 clients total, average of 148 clients per facility with 50% cluster size variation) to detect a significant difference in incident unintended pregnancy at the six-month follow-up. We assumed a binomial outcome as it is unlikely women will experience more than one unintended pregnancy within the six-month follow-up window.

Although the commonly accepted threshold is alpha = 0.05, we chose a threshold of alpha = 0.15 as acceptable for a reduction in unintended pregnancy for the present study to balance the study cost (to power the study at alpha = 0.05, the required sample size would be approximately 22,000 clients) with the Kenya MOH’s priorities, which required a focus on unintended pregnancy as the primary outcome. The MOH views 85% certainty that an observed reduction in unintended pregnancy is a true effect as reaching practical significance for guiding health policy. This approach aligns with an ever-growing consensus among statisticians that p-values should be viewed as continuous, and always considered within the context of related prior evidence, plausibility of mechanism, and stakeholder perspectives regarding risk vs. benefits of action based on the implicated change [15]. Additionally, this sample size is sufficient to show significant change among secondary outcomes at alpha = 0.05 based on results from the prior trial.

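### The figure of about 22,000 clients at alpha 0.05, offered as the cost reason for alpha 0.15, does not follow from the stated design assumptions

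*Protocol article*

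**What the plan says.** All of this is in the protocol article, section Power and sample size, except the number of facilities (24, 12 per arm), which is in Design overview.

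- Effect: unintended pregnancy in the previous trial "was 1.72% among those receiving ARCHES and 3.13% among those receiving standard-of-care FP care (AOR 0.54"). The new trial is described as "powered to detect an AOR of 0.54 in unintended pregnancy in the intervention group compared to the control group at an alpha of 0.15".
- Clustering and loss: "assuming intra-class correlation of 0.1 from the previous trial (unpublished"), with 80% retention at six months.
- Result: "1770 FP clients are needed at baseline enrollment per study arm", that is "3540 clients total, average of 148 clients per facility with 50% cluster size variation".
- Reason for the threshold: "we chose a threshold of alpha = 0.15 as acceptable for a reduction in unintended pregnancy for the present study to balance the study cost", supported by the statement that "to power the study at alpha = 0.05, the required sample size would be approximately 22,000 clients".

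The section also reports the Ministry's view that 85% certainty is enough for policy. It does not give the power, the sidedness, the scale of the ICC, or whether the 22,000 keeps 24 facilities or keeps 148 clients per facility.

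**The concern.** Going from 3540 to 22,000 is a 6.2-fold rise (22,000/3,540). If facilities are added at the same size, the design effect cancels. Moving alpha from 0.15 to 0.05 at 80–90% power, with the same sidedness, should then cost less than a doubling. A 6-fold rise therefore needs some further assumption that the section does not state.

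The 22,000 is the only quantified cost given for tripling the type I error of the primary test. Anyone reading a primary result declared at alpha 0.15 will judge that threshold partly on this figure.

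**Working it through.** **Inputs.** p1 = 0.0172, p2 = 0.0313 (crude odds ratio 0.542, matching the stated 0.54). ICC 0.1; CV 0.5; retention 0.8; 12 facilities per arm. Retained per arm 1770 × 0.8 = 1416, so m = 1416/12 = 118 per facility. Power and sidedness are not stated. I assume 80% (range 80–90%) and try both sidednesses.

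**Formulas.** Pooled two-proportion size per arm: n = [z_α√(2p̄q̄) + z_β√(p1q1 + p2q2)]² / (p2 − p1)², with p̄ = 0.02425. Design effect: D = 1 + ((1 + CV²)m − 1)·ICC. Total enrolled = 2nD/0.8. Two-sided powers count only rejections in favour of ARCHES.

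**1. Does 3540 reproduce?** D = 1 + (1.25 × 118 − 1) × 0.1 = 15.65. Effective size is 1416/15.65 = 90 per arm. Power at alpha 0.15 is 20.5% two-sided or 33.7% one-sided. For 80% power at the same facility size, the totals are about 48,400 and 32,800. So it does not.

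**2. Individual n at alpha 0.05, 80% power.** Two-sided: (1.960 × 0.2175 + 0.842 × 0.2173)² / 0.0141² ≈ 1,870 per arm. One-sided: (1.645 × 0.2175 + 0.842 × 0.2173)² / 0.0141² ≈ 1,470.

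**3. ICC 0.1, 24 facilities kept.** As m grows, effective size per arm tends to 12/(1.25 × 0.1) = 96. This is far below 1,870 or 1,470, so no number of clients is enough. With 22,000 enrolled (8,800 retained per arm), effective size is 95, and power at alpha 0.05 is 9% two-sided or 16% one-sided.

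**4. ICC 0.1, more facilities of the same size.** Two-sided: 2 × 1,867 × 15.65/0.8 ≈ 73,000. One-sided: 2 × 1,471 × 15.65/0.8 ≈ 57,500. If power is instead set to what 3540 gives at alpha 0.15 (step 1), the totals are about 12,000 (two-sided) and 14,000 (one-sided).

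**5. Same facility size, any ICC.** D cancels, so only the ratio of the individual n matters:

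| Power | Two-sided | One-sided |
|---|---|---|
| 80% | 1.51 | 1.75 |
| 85% | 1.46 | 1.67 |
| 90% | 1.42 | 1.59 |

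**6. 24 facilities fixed, ICC left free.** Required m = n(1 − ICC)/(12 − 1.25·n·ICC), and total = 24m/0.8.
- One-sided, ICC 0.006: D = 1.879, effective size 754, power 77% at alpha 0.15. The same power at alpha 0.05 needs n = 1,357, so m = 1,357 × 0.994/(12 − 10.18) ≈ 740 and the total is about 22,200.
- Two-sided, ICC 0.007: D = 2.03, effective size 699, power 61%. The same power at alpha 0.05 needs n ≈ 1,188, so m ≈ 736 and the total is about 22,070.

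With sidedness held, the printed pair therefore appears only with facilities fixed and an ICC some 14 to 17 times below the printed 0.1 (0.1/0.007, 0.1/0.006).

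**7. Power of 3540 at the two thresholds.**

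| Basis | Alpha 0.15 | Alpha 0.05 |
|---|---|---|
| ICC 0.1, two-sided | 20% | 9% |
| ICC 0.1, one-sided | 34% | 15% |
| ICC 0.006, one-sided | 77% | 55% |
| ICC 0.007, two-sided | 61% | 40% |

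**The case against.** The trial has 24 facilities, and with facilities fixed a rise well above 1.5-fold is normal, because extra clients per facility add less and less. Step 6 shows that one reading can give both 3540 and about 22,000. The primary analysis is a mixed-effects logistic model, so the 0.1 may be on the latent scale. That would correspond to about 0.007 at 1.72% and 0.013 at 3.13% on the proportion scale, and the lower end meets the region in step 6. This stands, and it is why the point cannot be put as a 1.5-fold rise misreported as 6-fold. It does not rescue the figure: the article does not give that scale or that power, and the implied power is below 80%.

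Mixing sidedness (one-sided 0.15 against two-sided 0.05) also produces the pair. With ICC 0.1 and the same facility size it gives about 22,100, but at 34% power. With 24 facilities it gives 22,000 at about 82% power, but with ICC near 0.004. The first is not a powered design, and the second again needs an ICC that is not stated.

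A reader might infer that 22,000 is overstated about 4-fold, since an ICC near 0.001 with a two-sided test at 80% power reproduces 3540 and then gives about 5,340 (same facility size) or 5,770 (24 facilities) at alpha 0.05. The document supports neither that ICC nor that power. Because 3540 itself fails at ICC 0.1, 1.5 × 3540 is not a corrected requirement. At the printed ICC, 22,000 is too low.

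Finally, the 22,000 is a counterfactual in parentheses. It sets no enrolment, test or estimate, and the Ministry's 85% view is a separate reason for alpha 0.15. That limits the consequence, but this is a printed number in conflict with printed inputs, not detail that an article leaves out.

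**Conclusion.** The concern holds in this form: with the stated rates, ICC 0.1, CV 0.5, 80% retention and either 24 facilities or 148 clients per facility, about 22,000 is not the size needed at alpha 0.05 for 80% power, one-sided or two-sided. The stated inputs lead to no attainable number (24 facilities) or to about 57,500–73,000 (same facility size).

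The direction of the error is open. It depends on power, sidedness, the ICC and its scale, and what is held fixed, none of which is settled by the text. The results rest on the pooled normal approximation and the usual design effect for unequal clusters. The gaps at the printed ICC are too large for a refinement of either to close. A reader might also suppose that the ethics committees approved the threshold on the strength of this cost. The article lists their approvals but does not say what they were shown.

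**What to change.** In Power and sample size, state the power, the sidedness, the ICC with its scale, and whether facilities or clients per facility would be increased. Recompute both 3540 and the alpha 0.05 requirement on that single basis, and replace the 22,000. If 24 facilities cannot reach the target at alpha 0.05, say so instead of giving a number. Report the power of 3540 at alpha 0.05 next to that at 0.15, and restate the reason for alpha 0.15 on those figures. The cost is a short recalculation and a change of wording. Enrolment need not change.

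### Alpha 0.15 is presented as 85% certainty that an observed reduction is real, which it does not give; the 22,000-client alternative offered in its support is not reproducible from the stated ICC at conventional power

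*Protocol article*

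**What the plan says.** All of this stands in the protocol article, section Power and sample size. On the threshold: "we chose a threshold of alpha = 0.15 as acceptable for a reduction in unintended pregnancy". Two reasons follow. The first is cost: "to power the study at alpha = 0.05, the required sample size would be approximately 22,000 clients", against the 3540 planned. The second is what the threshold is taken to mean: "The MOH views 85% certainty that an observed reduction in unintended pregnancy is a true effect as reaching practical significance for guiding health policy". The next sentence adds that p-values should be read as continuous and weighed with prior evidence, mechanism and stakeholder views.

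The inputs come from the earlier Nairobi trial. Incident unintended pregnancy "was 1.72% among those receiving ARCHES" and "3.13% among those receiving standard-of-care FP care (AOR 0.54) (unpublished"). The size is calculated "assuming intra-class correlation of 0.1 from the previous trial (unpublished"), with 80% retention, about 148 clients per facility and 50% cluster size variation. The Design overview gives 24 facilities, 12 per arm. No prior and no posterior calculation is given.

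**The concern.** One minus alpha is a statement about data given no effect. Certainty that an observed reduction is true is a statement about the effect given the data. The second cannot be read off the first without power and a prior.

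The sentence matters because it is offered as the reason why 0.15 is adequate for the primary outcome, and the Dissemination section says that the results will inform whether and how the model is scaled to other counties. A policy reader could take a result that just meets the threshold as 85% sure.

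The 22,000 is the other support for the relaxed alpha. If it does not follow from the plan's inputs, readers are weighing 0.15 against an alternative that has not been established.

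**Working it through.** **Inputs (Power and sample size; Design overview).** Rates 3.13% and 1.72% (crude OR 0.542, which agrees with the stated 0.54); ICC 0.1, read on the proportion scale; cluster size variation CV 0.5; 148 enrolled per facility, so 148 × 0.8 ≈ 118 at six months; 12 facilities per arm. The article states neither power nor the side of the test, so I used 80% and 90% power and both sides.

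**1. The plan's own 3540.**
- Design effect = 1 + [(1 + CV²)m − 1] × ICC = 1 + (1.25 × 118 − 1) × 0.1 = 15.65.
- Effective n per arm = 12 × 118 / 15.65 = 90.5.
- Power at alpha 0.15 (two proportions, pooled variance) = 20.5% two-sided, 33.7% one-sided.

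So 3540 is not reproduced with ICC 0.1 at conventional power. It comes out exactly if clustering is ignored (one-sided 0.15, 90% power, continuity correction: 1416 / 0.8 = 1770 per arm). It comes out within 3% (3477) if 0.1 is read as a between-cluster coefficient of variation, two-sided at 80% power.

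**2. Probability that a significant reduction is real.** This is prior × power / [prior × power + a × (1 − prior)], where a is the chance of a significant reduction under no effect: 0.075 two-sided, 0.15 one-sided. The priors are my assumptions. Example, two-sided at an even prior: 0.1025 / (0.1025 + 0.0375) = 0.73.

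| Power | Test | Prior 0.5 | Prior 0.3 |
|---|---|---|---|
| 20.5% | two-sided | 73% | 54% |
| 33.7% | one-sided | 69% | 49% |
| 80% | two-sided | 91% | 82% |
| 80% | one-sided | 84% | 70% |

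At the power that the plan's inputs give, reaching 85% needs a prior of about 0.67 (two-sided) or 0.72 (one-sided).

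**3. The 22,000 at alpha 0.05.**

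*Facilities fixed at 24.* However many clients are enrolled, effective n per arm cannot exceed 12 / (1.25 × 0.1) = 96, or 12 / 0.1 = 120 with equal cluster sizes. Power at alpha 0.05 is then at most 9–17%, so no number of clients suffices.

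*Facilities added at the same size.* Total N = 2 × n × 15.65 / 0.8, where n is the per-arm size without clustering.

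| Test, power | n at 0.15 | N at 0.15 | n at 0.05 | N at 0.05 | Ratio |
|---|---|---|---|---|---|
| one-sided, 80% | 839 | 32,826 | 1,471 | 57,553 | 1.75 |
| one-sided, 90% | 1,278 | 50,002 | 2,037 | 79,698 | 1.59 |
| two-sided, 80% | 1,238 | 48,437 | 1,868 | 73,086 | 1.51 |
| two-sided, 90% | 1,761 | 68,899 | 2,500 | 97,812 | 1.42 |

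With equal cluster sizes the range at 0.05 is 46,704 to 79,375. The article implies a ratio of 22,000 / 3540 = 6.2. Even one-sided 0.15 set against two-sided 0.05 gives only 2.0 to 2.2.

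*Carrying forward the two routes that match 3540.* At alpha 0.05 they give 5,443 to 6,600 (clustering ignored) and 5,329 (coefficient of variation).

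*What does come near 22,000.* Keep 24 facilities, back-solve the ICC that yields 3540, and set one-sided 0.15 against two-sided 0.05. At 82% power the ICC is 0.0038 and N is about 23,000. The answer is very sensitive to power: about 54,000 at 80% and 12,900 at 85%. Other near-matches need 33.7% power with facilities added (22,106), or a logit-scale ICC with equal cluster sizes and 62–76% power (16,873 to 28,232).

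**The case against.** The case against has several parts.

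- *The sentence reports the Ministry's tolerance, and the next one warns against mechanical use of p-values.* That is so, and nothing says that a p just under 0.15 will be reported as 85% sure. A reader might infer such a rule, but the article does not lay one down. The wording still ties 0.15 to 85% certainty, and the remark about prior evidence names exactly what 1 minus alpha leaves out.
- *The figure is not always too high.* This stands. Two-sided at 80% power with an even prior gives 91%. The low figures come largely from what ICC 0.1 does to power, which is a sample-size problem in its own right. Under a flat prior and a normal approximation, P(OR < 1) at one-sided p = 0.15 is 0.85, and at two-sided p = 0.15 it is 0.925. So 85% can be defended as a posterior probability, but only under a prior that the article does not state. Earlier ARCHES trials might also support a prior above 0.5.
- *Unstated assumptions might give 22,000.* This also stands in part. One might infer that no assumptions reach it; the last step of the working shows otherwise. Those routes need an ICC far below 0.1 on the proportion scale, or a different ICC scale, or power below convention, so they do not rescue the stated inputs.
- *Side and power are commonly left to the full protocol or analysis plan.* Agreed: their absence from the article is not part of this point.

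**Conclusion.** The point holds in this form: alpha 0.15 does not carry 85% certainty that an observed reduction is true. Over the assumed priors of 0.3 and 0.5, that probability is about 49–73% at the power which the plan's inputs give, and 70–91% at 80% power. The documents do not support the stronger statement that 85% is always an overstatement; it depends on side, power and prior, so it is not a property of the rule.

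The 22,000 is not reproducible from ICC 0.1 at 80–90% power and is inconsistent with 3540. It does not follow that the figure is impossible under any assumptions. This limb rests on a proportion-scale ICC and CV 0.5. The certainty limb does not depend on it: 1 minus alpha would be misread whatever the sample size.

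**What to change.** 1. Describe 0.15 as a type I error rate, for example: *if ARCHES had no effect, a result meeting the threshold would still occur with probability 0.15.* Remove the equation with 85% certainty.
2. Report the odds ratio for unintended pregnancy with 85% and 95% intervals.
3. If the Ministry wants a certainty statement, report P(OR < 1) from the same mixed model with its prior stated. The choice of prior is for the investigators and the Ministry.
4. Recompute the 22,000 and give its assumptions beside it (power, side, ICC and its scale, number of facilities), or delete it.

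The cost is wording, one recalculation and, if wanted, one added model output. Neither the design nor the primary model changes. The downside is that the certainty claim and the cost argument for 0.15 become less favourable.

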### Allocation

A total of 24 government health facilities in Uasin Gishu county were randomly selected for study participation. This cluster-randomized controlled trial used parallel assignment to two arms: (1) the intervention arm will implement the ARCHES intervention integrated in the BCS + counseling strategy, and (2) the control arm will implement standard contraceptive care using the BCS + approach. Researchers at UCSD compiled a list of the 24 facilities and stratified based on facility type (hospital, health center, or dispensary) and urban or rural location, and used SAS to generate random numbers to randomize an equal number of facilities to the intervention and control groups within these strata. All FP clients enrolled in facilities assigned to the intervention group are considered intervention group participants, and all FP clients enrolled in facilities assigned to the control group are considered control group participants.

### Participants

#### Ethics approval

This study has been approved by the University of California, San Diego Institutional Review Board (IRB) (Protocol Number: 201922S), the Population Council IRB (Protocol Number: 969), and the Kenyatta National Hospital/University of Nairobi Ethics Review Committee (Protocol Number: P369/05/2021).

#### Protocol amendments

Substantive modifications to the study protocol that impact the study procedures will be approved by the three ethics committees through formal amendments prior to implementation.

#### Recruitment

Female FP clients will be recruited from all 24 health facilities selected for the evaluation trial (n = 3540). Women and girls visiting the clinic and directed to the FP counseling station will be recruited by a research assistant (RA) hired and trained by Population Council Kenya. The RA will ask clients if they would be interested in hearing about a women’s health study being conducted at the clinic. If the client is interested, the RA will accompany the client to a separate, private room. The RA will describe the study to see if the client is interested in hearing more. If the clients expresses interest in hearing more about the study, the RA will begin eligibility screening. If eligible, the RA will administer informed consent, explaining the study, including the nature of the study, what their participation would entail, the compensation structure, and follow-up data collection. All screened potential participants will be provided with an information sheet that includes available community and health resources, including service information for local IPV services. Given the volume of FP clients seen at each selected health facility, recruitment is expected to last 2–3 months to enroll the approximately 148 FP clients required from each study site.

#### Eligibility

For female FP clients, eligibility criteria will include being: A) A health facility client seeking voluntary FP services, B) Aged 15–49 years old, C) Female, D) Able to provide informed consent, E) Able to speak and understand English, Kiswahili, or Kalenjin, F) Not sterilized (self-report), G) Not currently pregnant at baseline (self-report), H) Able to provide a safe phone number at which they can be recontacted for follow-up, and I) Not planning to move out of the area in the coming 6 months. FP providers must be A) Above age 18, B) Practicing MOH FP provider at health facility selected for intervention delivery, and C) Participate in the ARCHES FP provider training. Providers asked to participate in follow-up interviews or FGDs must have delivered ARCHES FP services to at least 25 clients.

#### Informed consent

Informed consent will be obtained in a private area in the health facility by the trained RA before any survey administration, interviews, or FGDs are conducted. As described above, participants will be notified of the purpose of the study, what is entailed in their participation, the risks and benefits of participating in the study, and clarify that participation is voluntary, consent can be withdrawn at any time during the study, there are no consequences for withdrawing from the study, and their participation is in no way tied to their ability to receive clinical services at the health facility or employment at the health facility (see Additional File 2 for Model Consent Form). Moreover, it will be reiterated at multiple points in the survey (e.g., before survey sections on any sexual behaviors or experiences of violence) that a participant is free to decline to answer any question they wish and may terminate the interview at any time. When obtaining consent for interview audio recordings, it will also be stated (and the consent form will indicate) that the recordings may be stopped at any time and that portions and/or the entire audio may be erased upon request. The RAs will be carefully trained not to apply pressure, to give the client space to express their concerns and address them, and to recognize if a participant is experiencing distress because of participating in the focus group, interview, or survey. Consent forms will be written in Kiswahili and English, and participants will provide a signature or mark to indicate their consent. In the case of women and girls who are illiterate or those who speak Kalenjin and cannot read in Kiswahili or English, we will read the consent form aloud and then question potential participants about points made in each paragraph of the consent (illiterate participants will provide a mark on the consent form rather than a signature).

We have obtained a waiver of parental consent for female FP clients aged 15–17 years old. Females aged 15–17 years (minors) are a critical population to include in this study due to their vulnerability to RC, IPV and poor reproductive health outcomes. In Kenya, minors are legally permitted to access reproductive health services without parent permission to protect their confidentiality and safety; requesting parental permission for participation in the current study (in which participation is highly connected with receipt of FP services) would be a breach of their right to confidentiality and could results in increased social and physical risk. These risks are intensified in this sensitive study about unintended pregnancy and familial/partner violence. This study also falls under the purview of the Code of Federal Regulations 45 CFR 46.408(c) and 46.116(d) which provide provisions for waiving parental permission in the case that the research providers no more than minimal risk to subjects, the waiver will not adversely affect the rights and welfare of the subjects, the research could not be practically carried out without such alteration, and that subjects will be provided with all necessary information, all of which apply to this study.

There will be no required alternative treatments or procedures for potential participants who are ineligible or decline participation in the ARCHES Kenya research. FP clients will receive the ARCHES Kenya intervention at the 12 intervention health facilities and will receive standard FP counseling services at the 12 control health facilities regardless of participation in the research per MOH protocols. Additionally, all screened potential participants will be provided with an information sheet that includes available community and health resources, including service information for IPV service providers.

